### 6.3.2. All observations after first month

The following items will be observed or evaluated according to the observation schedule:

- Observation status: Ongoing or unavailable
- Date of observation (date of last information if unavailable for observation)
- Presence or absence of events
  - If events have occurred, refer to 6.3.3. *Events*.
- Presence or absence of adverse events or serious adverse events
  - If events have occurred, refer to 23. *Procedures for Adverse Events* and 24. *Evaluation of Adverse Events*.
- Modified Rankin Scale (mRS)
- Status of study drug administration
  - Administration rate:  $\geq 70\%$  or  $< 70\%$
  - Withdrawal ( $< 4$  weeks of continuous drug withdrawal): No or Yes (length)

Discontinuation ( $\geq 4$  weeks of continuous discontinuation): No or Yes (date and reasons)

- Drugs used other than study drugs
- Blood pressure

### 6.3.3. Events

If any event described below occurs, the information below must be reported.

Refer to 23. *Procedures for Adverse Events* and 24. *Evaluation of Adverse Events* for information that must be reported in case of serious adverse events.

If a subject is transported to another medical institution due to an event, the following information will be obtained through cooperation from the subject or family, etc., then entered into medical records and used as reference materials.

#### Death

Date, cause, and rationale for cause

#### Ischemic stroke (IS)

Date

Clinical subtype: lacunar, atherothrombotic, or other

Responsible lesion: supratentorial, infratentorial, or both

#### Intracerebral hemorrhage (ICH)

Date

#### Subarachnoid hemorrhage (SAH)

Date

#### TIA

Date

#### Myocardial infarction (MI)

Date

#### Other vascular events\*

Date and details

\* e.g. aortic dissection or rupture; pulmonary embolism; heart failure, angina pectoris, or occlusive arteriosclerosis requiring hospitalization; and revascularization of coronary artery, aorta, peripheral artery, etc.

## 7. Adverse Events

### 7.1. Definition

#### 7.1.1. Adverse events

Adverse events are any medically undesirable event observed in a subject who has received a study drug, even if the causal relationship is not known.

In other words, adverse events are any undesirable or unintended sign (including abnormal laboratory values),

symptom, or illness observed under treatment with a study drug, regardless of causal relationship with the treatment.

Aggravation of any symptom, sign, or disease preexisting granting of consent or start of observation, will be handled as a new adverse event.

### **7.1.2. Serious adverse events**

Serious adverse events are adverse events for which any of the following apply:

1) Fatal

2) Life-threatening

The term "life-threatening" refers to an event in which the subject was at risk of death at the time of the adverse event; it does not refer to an event which hypothetically might have caused death if it were more severe.

3) Requires hospitalization or prolongation of existing hospitalization for treatment

4) Results in persistent or significant disability/incapacity

5) Is a congenital anomaly/birth defect

6) Other conditions, i.e., a medically important event for which treatment is required to avoid risks or items 1)–5) above, even if the event is not immediately life-threatening, or resulting in death or hospitalization. Examples include bronchospasm requiring intensive care in emergency rooms etc.; blood disorder or convulsions not leading to hospitalization; and drug dependence or abuse.

Explanation of "hospitalization for treatment" for serious adverse events

"Hospitalization for treatment" is defined as hospitalization of a subject in a medical institution (usually for at least one night) for treatment of adverse events, even if no particular treatment is performed (resting cure). This does not include hospitalization for examination or treatment of the primary disease or complications not aggravated from pre-observation conditions; hospitalization for convenience or personal reasons not intended to treat adverse events; and hospitalization for treatment or examination that was already scheduled prior to the first visit.

## **7.2. Procedures for adverse events**

Refer to 23. *Procedures for Adverse Events*.

## **7.3. Evaluation of adverse events**

Refer to 24. *Evaluation of Adverse Events*.

## **7.4. Follow-up of adverse events**

Refer to 25. *Follow-Up Investigation of Adverse Events*

### 7.5. Expected adverse drug reactions

Refer to the package insert of study drugs for expected adverse drug reactions and precautions.

### 7.6. Procedures for subjects who are suspected or known to be pregnant

Patients of childbearing potential are excluded from the study. However, an investigator/subinvestigator will conduct pregnancy tests during the observation period for subjects suspected to be pregnant. If the result is positive, the subject must discontinue study participation. Otsuka Pharmaceutical co., Ltd. must be informed of the matter if the pregnant subject was in the DAPT group. If the subject withdraws from the study, tests performed at discontinuation will be performed to the extent that the pregnancy is not adversely affected. Furthermore, follow-up investigation of the subject will continue until birth or termination of the pregnancy. For subjects in the DAPT group, follow-up results must be reported to Otsuka Pharmaceutical co., Ltd..

## 8. Efficacy Evaluation

### 8.1. Primary endpoint

The following is the study's primary endpoint:

- Recurrence of symptomatic ischemic stroke (with symptoms lasting for at least 24 hours)

### 8.2. Secondary endpoints

The following items are secondary endpoints:

- Any stroke [ischemic stroke (IS), intracerebral hemorrhage (ICH), or subarachnoid hemorrhage (SAH)]
- ICH or SAH
- Ischemic cerebrovascular disorder [IS or transient ischemic attack (TIA)]
- Death from any cause
- Stroke [IS, ICH, SAH], myocardial infarction (MI), or vascular death
- All vascular events: stroke, MI, and other vascular events [e.g. aortic dissection or rupture; pulmonary embolism; heart failure, angina pectoris, or occlusive arteriosclerosis requiring hospitalization; and revascularization of coronary artery, aorta, peripheral artery, etc.]

## 9. Safety Evaluation

The following are safety endpoints:

- Adverse events and adverse drug reactions
- Severe or life-threatening hemorrhage (GUSTO criteria)

## 10. Target Sample Size and Study Period

### 10.1. Target sample size

4,000 (2,000 per group)

## 10.2. Study period

The subject enrollment period lasts until target sample size is met. This period is planned to last from October 2013 to March 2017.

Study period lasts until 1 year after the first observation day of the last subject enrolled. This period is planned to last from October 2013 to March 2018.

## 11. Statistical Analysis

### 11.1. Rationale for target sample size

We assumed an annual recurrence rate of 4% in the monotherapy group based on data from the EVEREST study and the aspirin monotherapy group in the JASAP study. We also assumed a 30% decrease in relative recurrence risk (in other words, an annual relapse rate of 2.8%) in the DAPT group with cilostazol. The number of subjects required was calculated at 1,688 per group using the methods described by Lakatos et al in our main analytical method of the log-rank test (conditions were assumed relapse rates for each group, a 2.5 year enrollment period, a maximum 3.5 year observation period,  $\alpha=0.05$ , and a statistical power of 80%). This results in a total target sample size of 4,000 (2,000 per group), assuming an annual dropout rate of 5% during the study period.

### 11.2. Analysis populations

The intent-to-treat (ITT) analysis population used for evaluating safety and efficacy is defined as all randomly allocated study subjects. In compliance with the CONSORT Statement, we will create a flow diagram containing numbers of enrolled subjects, randomly allocated subjects, subjects observed for 1 year, subjects observed for 2 years, etc.

### 11.3. Analysis items and methods

Demographic characteristics of patient backgrounds will be calculated for each group in the ITT analysis population. Continuous variables are shown as mean (standard deviation) or median (quartile ranges), while category variables are shown as number of subjects (percentage) per category. Mean and median values will also be calculated for length of subject observation periods. Intergroup bias will also be studied with appropriate tests based on variable characteristics.

Kaplan-Meier plots will be drawn by group for the primary endpoint of ischemic stroke recurrence, while groups will be compared with the log-rank test. Also, the Cox proportional hazards model will be used to calculate hazard ratios and 95% CIs for DAPT groups versus SAPT groups. Unadjusted hazard ratios and adjusted hazard ratios [adjusted according to age, sex, clinical type of cerebral infarction (atheroma or lacunar), and mRS] will be calculated at this time.

Annual recurrence rates will be calculated with both person-year and Kaplan-Meier methods, 95% CIs for which will be calculated with the approximate Poisson and Greenwood methods.

Subgroup analysis will include the following factors: age, sex, antiplatelet therapy (aspirin or clopidogrel), clinical subtype of ischemic stroke (atheroma or lacunar), presence or absence of 50% or greater stenosis of

extracranial arteries, mRS, medical history and complications (hypertension, diabetes mellitus, dyslipidemia, coronary heart disease, peripheral artery disease, chronic kidney disease, and ischemic stroke), smoking status, and BMI. Continuous variables will be divided at the median, at which point a Cox proportional hazards model including a comparison group, predictive factors, and interactions will be studied. Stratified hazard ratios of the combination group compared to the SAPT group will be calculated according to predictive factors. Uniformity of interactions will also be studied. Significance level for all statistical tests is bilateral 5%.

Details of statistical analysis are described in the statistical analysis protocol authored by the Statistical Analysis Committee and the analysis officers in charge of the final analysis in the data center.

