## 6.8 Subgroup analysis

A subgroup analysis will be performed for the primary endpoint, using the variables shown in Table 6.8 as stratification variables. A Cox proportional hazard model for the primary endpoint that includes a comparison group and predictive factors will be examined. The hazard ratio for the combination therapy group versus the monotherapy group will be calculated for each stratification category based on the predictive factors. Uniformity will be examined for the stratification categories.

Table 6.8: Stratification Variables

| Item                                 | Category                                   |
|--------------------------------------|--------------------------------------------|
| Sex                                  | Male, Female                               |
| Age (yr)                             | up to 49, 50 to 59, 60 to 69, 70 and older |
|                                      | up to 64, 65 and older                     |
| BMI                                  | < 25, ≥ 25                                 |
| Past history and concomitant disease |                                            |
| Coronary artery disease              | No, Yes                                    |
| Peripheral artery disease            | No, Yes                                    |
| Hypertension                         | No, Yes                                    |

|                                                            |                           |
|------------------------------------------------------------|---------------------------|
| Diabetes mellitus                                          | No, Yes                   |
| Dyslipidemia                                               | No, Yes                   |
| Chronic renal disease                                      | No, Yes                   |
| History of symptomatic ischemic stroke                     | No, Yes                   |
| Habitual smoking                                           | No, Yes                   |
| Antiplatelet drugs *1                           | aspirin, clopidogrel      |
| Ischemic stroke clinical subtype                           | lacunar, atherothrombotic |
| At least 50% stenosis of an extracranial artery            | No, Yes                   |
| Degree of independence in activities of daily living (mRS) | 0, 1, 2, 3, 4, 5, 6       |

\* 1: At start of observations

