## **9. EFFICACY EVALUATION**

### **9.1 Primary endpoint**

The first recurrence of ischemic stroke between the first and last observation days (during the observation period) will be included in the analysis.

Subjects discontinued for reasons other than occurrence of the primary endpoint and subjects who continue to study completion will be treated as censored subjects. The censor date will be considered the observation completion date.

- 1) A between-groups comparison for the period from the observation start date to the date of ischemic stroke recurrence will be performed using the log-rank test, and the superiority of the combination therapy group versus the monotherapy group will be examined.
- 2) Survival coefficients for the period from the observation start date to the date of ischemic stroke recurrence will be estimated for each treatment group using the Kaplan-Meier method and plotted.
- 3) The hazard ratio for ischemic stroke recurrence in the combination therapy group versus the monotherapy group and its 95% confidence interval will be determined using a Cox proportional hazard model.
- 4) An adjusted hazard ratio will be calculated using a Cox proportional hazard model that includes as covariates age (each 1 year), sex, ischemic stroke clinical subtype (atheromic, lacunar, other, unknown), mRS (ordered categorical data).
- 5) The annual incidence in each group will be calculated using the person-year and Kaplan-Meier methods. The 95% confidence interval of the incidence will be calculated using the approximate Poisson method and the Greenwood method. One year will be considered 365.25 days for the calculations.

- 6) A subgroup analysis will be performed for each variable shown in Table 6.8 using a Cox proportional hazard model that includes a comparison group and predictive factors. The hazard ratio for the combination therapy group versus the monotherapy group will be calculated for each stratification category based on the predictive factors. Uniformity will be examined for the stratification categories based on the interaction between the comparison group and predictive factors.
- 7) Frequency distributions for each treatment group will be determined for the findings regarding the clinical subtype of ischemic stroke (lacunar, atherothrombotic, other, unknown) and responsible lesion (supratentorial, infratentorial, both, unknown) at the time of ischemic stroke onset.

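### Treatment interactions for age and BMI are tested only on cut values, which costs about 10 to 20 points of power on a supportive test that is already weak

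*Supplement*

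**What the plan says.** Protocol v1.3 section 11.3 lists age and BMI among the subgroup factors and sets one rule for continuous factors: "Continuous variables will be divided at the median, at which point a Cox proportional hazards model including a comparison group, predictive factors, and interactions" are to be studied. It leaves the details to the statistical analysis plan.

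The SAP does not carry the median rule forward. Table 6.8 in section 6.8 groups age twice, as "up to 49, 50 to 59, 60 to 69, 70 and older" and as "up to 64, 65 and older", and cuts BMI at 25. Section 9.1 item 6 then says: "Uniformity will be examined for the stratification categories based on the interaction between the comparison group and predictive factors". The SAP does not say which of the two age groupings supplies the interaction test.

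Both factors are held as continuous values. Age is derived from the dates of birth and consent (SAP 6.2.1), and BMI from height and weight (SAP 6.2.2). For covariate adjustment the SAP already uses age on its natural scale, in section 9.1 item 4: "An adjusted hazard ratio will be calculated using a Cox proportional hazard model that includes as covariates age (each 1 year), sex". That model has main effects only. No continuous treatment-by-age or treatment-by-BMI term appears in either document, and no power is given for any interaction test.

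**The concern.** Cutting a continuous effect modifier before testing it treats patients within a band as identical. If the effect of adding cilostazol drifts with age or BMI, the drift inside each band is lost to the test. Four unordered age bands also spread the question over 3 degrees of freedom.

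Interaction tests have far less power than the main comparison, so there is little to spare. A non-significant banded result could be read as evidence that the effect is the same across age or BMI when the test had little chance of showing otherwise. A test on the uncut values uses data already in hand.

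**Working it through.** **Inputs from the documents.** Annual rates 4.0% and 2.8%, 2.5 years of enrollment, 3.5 years maximum observation, two-sided 5%, 80% power, 5% annual dropout (protocol 11.1); 2,000 per group (10.1); an expected 8,000 person-years (11.4.1).

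**Inputs assumed.** The documents give no age or BMI distribution. The ranges used are age mean 66-72, SD 8-10, and BMI mean 22.5-25, SD 3-4, both near-normal. The log hazard ratio is taken as linear in the factor.

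**1. The plan's own figure.** There is none for interactions, so the sample size was reproduced to confirm the design inputs.
- Events needed: 4 × (1.960 + 0.842)² / (ln 0.70)² = 247.
- Event probability at 4.0%: 1 − (e^−0.04 − e^−0.14)/(2.5 × 0.04) = 0.0857. At 2.8%: 0.0609. Mean 0.0733.
- Per group: 247 / 0.0733 / 2 = 1,685, against 1,688 stated. Freedman's formula gives 1,726 and a numeric Lakatos calculation 1,715, both within 3%.
- 1,688 / 0.95^k for k = 3 to 3.5 gives 1,969 to 2,020, consistent with 2,000.

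**2. Events available.** 8,000 × (4.0% + 2.8%)/2 = 272.

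**3. Continuous test.** With 1:1 allocation the standard error of the log ratio of hazard ratios per SD is 2/√272 = 0.121, so z = ln(ratio)/0.121.

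**4. Median split.** For a normal factor it keeps 2/π = 63.7% of the information, a loss of 36.3%, so z is multiplied by √0.637 = 0.798.

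| Ratio of HRs per SD | z continuous | Power | z median split | Power |
|---|---|---|---|---|
| 1.2 | 1.50 | 32% | 1.20 | 22% |
| 1.3 | 2.16 | 58% | 1.73 | 41% |
| 1.4 | 2.77 | 79% | 2.21 | 60% |

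An interaction with 80% power as continuous has 61% after the split.

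**5. The SAP's two-band cuts.** The share of information kept is φ(c)² / [p(1 − p)], where c is the standardised cut and p the share of patients below it. For age cut at 65 with mean 70, SD 9: c = −0.556, φ = 0.342, p = 0.289, so 0.1169 / 0.2056 = 0.569. Over the assumed ranges:
- Age at 65 loses 37-52%; 80% continuous power becomes 49-61%.
- BMI at 25 loses 36-51%; 80% becomes 50-61%.

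**6. The SAP's four age bands.** They lose only 15-30% of the linear information, but the 3-df test has 48-57% power where the continuous test has 80%.

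**7. Simulation check** (600 runs per setting, 4,000 patients, about 278 events, age mean 69 and SD 9.5 before truncation).

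| Ratio per SD | Continuous | Median split | Cut at 65 | Four bands |
|---|---|---|---|---|
| 1.2 | 28% | 24% | 21% | 22% |
| 1.3 | 54% | 40% | 36% | 34% |
| 1.4 | 73% | 57% | 52% | 50% |

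Monte Carlo error is about 2 points. The ordering agrees with the formulas. At the smallest ratio the simulated gap is 4-7 points rather than the formula's 10; at 1.3 and 1.4 it is 14-23 points.

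**The case against.** The strongest reply is that this is an optional refinement to a supportive analysis, and most of that stands.

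- **The 36% is the protocol's figure.** A reader might infer that the planned analysis loses about a third. The SAP holds the details and uses other cuts, so its loss is a range that rests on assumed distributions: larger for the two-band cuts, smaller for the four bands before the extra degrees of freedom.
- **Few events matter more than banding.** A reader might infer that banding is why real interactions would be missed. With 272 events, a slope of 0.15 in the log hazard ratio per SD gives about 23% power continuous and 17% split; at 0.10 it is about 13% and 10%. Both tests mostly miss effects of that size. Larger slopes show the gap better but are extreme: 0.35 per SD around a hazard ratio of 0.70 means 0.49 at one SD below the mean and 0.99 at one SD above. Nothing in the documents predicts that.
- **No decision hangs on these tests.** A reader might infer that they determine whether the effect is reported as uniform. SAP 6.8 and 9.1 say only that uniformity is examined. Hazard ratios are given for each category in any case, and SAP 6.6 adjusts only the primary endpoint for multiplicity.
- **Bands have merits.** They are prespecified, 65 is also an enrollment risk-factor threshold (protocol 3.2), and the p-value matches the displayed estimates. A true threshold at the cut would favour the banded test, and a linear term can miss a non-monotone pattern.
- **Extra models add flexibility.** A continuous test plus a spline check could leave several competing p-values. That is a fair criticism of any fix that does not name the governing one.

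None of this explains why age is kept per year for adjustment but cut for the interaction.

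**Conclusion.** The point holds as a cheap improvement, not as an error in the plan's inference. Both documents test the age and BMI interactions only on cut values. For moderate interactions (ratio of hazard ratios 1.2 to 1.4 per SD), the median split costs about 10-20 points of power by formula. The SAP's two-band cuts and its 3-df age test do no better than the median split across most of the assumed distributions.

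The size rests on a near-normal factor, a roughly log-linear interaction, about 272 events, and age and BMI distributions that the documents do not supply. The continuous test is itself weak, so a non-significant result should not be read as proof of a constant effect under either approach. The primary log-rank test, the main Cox estimate and the sample size are untouched.

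**What to change.** In protocol 11.3 and SAP 9.1 item 6, prespecify one governing interaction p-value for age and one for BMI: the 1-df product term in a Cox model containing treatment, the continuous factor (age per year, BMI per kg/m²) and their product.

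Keep the Table 6.8 bands to display hazard ratios. If a quadratic or spline term is added, label it a descriptive linearity check that does not replace the governing p-value. The same edit can reconcile the protocol's median rule with the SAP's fixed cuts and settle which age grouping is for display.

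The cost is a few lines of text and two extra model fits on data already collected, with no change in sample size. The downside is some loss of power if the true interaction is a threshold at the cut or is non-monotone.

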#### **11.4. Interim review**

##### **11.4.1. Interim review methods**

Because this study involves a long observation period, interim review will be performed in order to secure subject safety. An interim review of safety endpoints (serious adverse events, adverse drug events and hemorrhagic events), in principal, will be performed once per year. Besides the above reviews of safety endpoints, a review of efficacy and safety endpoints will also be performed once only during the study. The operation date, methods and others were described in “The Independent Data Monitoring Committee Procedure Manual” separately.

The interim review of safety and efficacy endpoints will be performed when 50% of information has been obtained (when 4,000 person-years of data have been collected, or specifically approximately when the 2.5 year enrollment period ends). The Haybittle-Peto ad-hoc method will be used for discontinuation criteria of primary endpoint. No specific discontinuation criteria will be established for safety endpoints, but the Independent Data Monitoring Committee (IDMC) will consider discontinuation or continuation based on incidence rates and make a recommendation to study investigators.

Timing of the interim review of safety and efficacy endpoints was determined based on planned enrollment period, observation period, and withdrawals/dropouts. Because the enrollment period for the study is 2.5 years and observation will end 1 year following the date of initiation of observation of the final subject to enroll, the observation period will last 3.5 years for the first subject to enroll and 1 year for the last subject to enroll. Assuming that subjects will enroll at a regular rate, mean observation period will last 2.25 years for 9,000 total person-years ( $4,000 \times 2.25$ ). However, given the possibility of withdrawals or dropouts, mean observation period is assumed to be 2 years, resulting in a likely total of 8,000 person-years ( $4,000 \text{ subjects} \times 2 \text{ years}$ ). Therefore, the review of safety and efficacy endpoints will occur at the mid-point up to 8,000 person-years, or when 4,000 person-years of data has been collected.

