## 6.5 Significance level and confidence coefficient

Because the evaluation of superiority with respect to the primary endpoint will be based on repeated tests, including the interim analysis, an increase in type I errors resulting from multiplicity will occur. Therefore, significance levels (two sided) will be selected using the Haybittle-Peto ad-hoc method.

Interim analysis significance level: 0.0027 (corresponds to  $z = 3$ )

Significance level for final analysis: 0.05

The significance level of the tests used in the other efficacy and safety evaluations will be a two-sided level of 5%. A two-sided significance level of roughly 5% will also be used for other evaluations, although an explicit significance level will not be established.

The confidence coefficient used for the estimates will be 95% (two sided).

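### Protocol v1.3 plans 3.5 years of enrolment, but the interim trigger is still derived from 2.5 years, so 4,000 person-years is about 41% of the information and not 50%

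*Supplement*

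**What the plan says.** Protocol v1.3, section 10.2, on enrolment: "The subject enrollment period lasts until target sample size is met. This period is planned to last from October 2013 to March 2017". On the whole study: "Study period lasts until 1 year after the first observation day of the last subject enrolled", with the end planned for March 2018 ("This period is planned to last from October 2013 to March 2018"). Section 10.1 keeps the target at 4,000, or 2,000 per group.

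Protocol v1.3, section 11.4.1, provides for one review of efficacy and safety at 50% of the information, and glosses that as "when 4,000 person-years of data have been collected, or specifically approximately when the 2.5 year enrollment period ends". The derivation that follows starts with "Because the enrollment period for the study is 2.5 years". It reaches a mean follow-up of 2.25 years (9,000 person-years), reduces this to 2 years for withdrawals (8,000 person-years), and closes by setting the look at 4,000 person-years.

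Section 11.1 bases the sample size on "a 2.5 year enrollment period, a maximum 3.5 year observation period". SAP section 6.5 sets the interim level at 0.0027 two-sided (z = 3) and then: "Significance level for final analysis: 0.05". The SAP preface says that the plan was prepared from protocol v1.2, before the dates were extended.

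**The concern.** Sections 10.2 and 11.4.1 are both current text of v1.3 and give different enrolment lengths. Every figure in the interim derivation (2.25 years, 9,000, 2 years, 8,000, 4,000) follows from the shorter one. A longer enrolment with the same 4,000 subjects and the same 1-year tail produces more follow-up, so 4,000 person-years is no longer half of it.

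The paragraph also treats three things as roughly one moment: half the information, 4,000 person-years, and the end of enrolment. On the v1.3 calendar they separate. This is the trial's only efficacy look with a stopping rule, so its timing should be fixed and correctly described before any comparative data are seen. Timing also changes the chance of stopping early if cilostazol works as assumed.

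**Working it through.** **Inputs.** N = 4,000 (10.1). Enrolment R = 2.5 years (11.4.1) or 3.5 years (10.2). Minimum follow-up F = 1 year (10.2). Uniform accrual and a reduction of the mean from 2.25 to 2 years, a factor of 8/9 (11.4.1). Annual rates of 4% and 2.8%, and 5% dropout per year (11.1).

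**1. The plan's figure reproduces.** Total person-years without attrition = N × (F + R/2) = 4,000 × (1 + 1.25) = 9,000. With the 8/9 factor this is 8,000, and 4,000/8,000 = 50%.

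**2. The same rule with R = 3.5.** 4,000 × (1 + 1.75) = 11,000 person-years. With the 8/9 factor this is 9,778, and 4,000/9,778 = 40.9%. Without attrition the share is 4,000/11,000 = 36.4%, to be compared with 4,000/9,000 = 44.4% on the old calendar. Half of the total is 5,500 person-years without attrition, or 4,889 with the factor.

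**3. Dates.** Without attrition, person-years by time t during enrolment are N t²/(2R). Setting 4,000 t²/7 = 4,000 gives t = √7 = 2.65 years. At t = 3.5 the sum is 7,000, or 64% of 11,000. With a constant exit hazard h, person-years by t ≤ R are (N t/R)(1/h)[1 − (1 − e^(−ht))/(ht)], and the total is (N/h)[1 − (e^(−hF) − e^(−h(R+F)))/(hR)]. For R = 3.5:

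| Attrition | Total | 4,000 as share | Date of 4,000 | Date of half | At 3.5 years |
|---|---|---|---|---|---|
| none | 11,000 | 36.4% | 2.65 y | 3.10 y | 7,000 (64%) |
| 5%/y dropout | 10,168 | 39.3% | 2.71 y | 3.06 y | 6,599 (65%) |
| dropout plus primary events (3.4%/y) | 9,667 | 41.4% | 2.75 y | 3.03 y | 6,352 (66%) |
| hazard fitted to the plan's 2-year mean (0.097/y) | 9,497 | 42.1% | 2.77 y | 3.02 y | 6,268 (66%) |

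With R = 2.5 and that fitted hazard, 4,000 person-years and half information coincide at 2.32 years, near the end of enrolment at 2.50. The gloss was a fair approximation on the old calendar.

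**4. Events.** Take hazards λ of 0.04 and 0.028 and a dropout hazard δ = −ln 0.95 = 0.0513. Expected events per group are 2,000 × λ/(λ+δ) × [1 − (e^(−(λ+δ)) − e^(−4.5(λ+δ)))/(3.5(λ+δ))]. This gives 191.7 + 136.5 = about 328, so half is 164, reached at about 3.03 years. At 2.75 years the expected count is about 136, and 136/328 = 41%, in line with the person-year share.

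**5. Power and stopping.** With 328 events, power is Φ(√(328/4) × |ln 0.70| − 1.96) = Φ(3.23 − 1.96) = about 90%. The chance of crossing z = 3 in favour of combination therapy at a hazard ratio of 0.70 is Φ(√(d/4) × 0.357 − 3): 18% at d = 136 and 24% at d = 164.

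**6. Type I error.** A z = 3 look followed by 0.05 (bivariate normal, correlation equal to the square root of the information share) gives an overall two-sided level of 0.0508 for a look at 50% and 0.0512 at 41%.

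**The case against.** The strongest reply is that the paragraph has an operative rule. It closes on 4,000 person-years, and the calendar phrase is only an approximate gloss. A reader might infer that the look could be held anywhere from about a third to two-thirds of the information. The text does not support that. The lower end takes the 2.5-year mark literally, and the upper end substitutes 3.5 years, which the sentence does not say. Under the closing rule the look is at about 41%.

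Section 11.4.1 also refers the operation date to a separate IDMC procedure manual, and 11.4.2 leaves details to an interim analysis protocol. Neither is shown, and either may fix the date. That is a fair limit on the practical risk. It does not repair the protocol, because no date can be at once 50% of the information and 4,000 person-years under the v1.3 calendar.

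The 36% figure should not be the headline. It leaves out attrition, which the plan's 50% includes; without attrition the plan itself stood at 44%.

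Person-years are not a wrong measure here. With constant rates the person-year and event shares agree at about 41%, so an event count is a preference and not a correction.

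Lastly, the shares depend on recruitment. With 3,000 subjects over 3.5 years the total is 8,250 person-years before attrition, and 4,000 is about 48% of it. That objection stands as a condition, but section 10.1 keeps the target at 4,000 and 10.2 runs enrolment until it is met.

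**Conclusion.** The point holds. Section 11.4.1 was not brought into line with section 10.2, and the stated 50% is about 41% on the plan's own method (39% to 42% across the attrition models tried, 36% with none). The three descriptions of the look are now spread over most of a year: 4,000 person-years at about 2.65 to 2.77 years, half information at about 3.0 to 3.1, and the end of enrolment at 3.5, when about 64% to 66% is in. These figures assume 4,000 subjects enrolled uniformly from October 2013 to March 2017 and followed to March 2018.

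The consequences are modest. An earlier look is less likely to stop the trial at z = 3 (18% against 24% under the design effect).

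Two stronger readings are not supported. A reader might infer that type I error is materially inflated, but the overall level is about 0.051 whether the look is at 41% or 50%. A reader might also infer that the sample size is now wrong. Section 11.1 is a valid record of the calculation that produced 1,688 per group, and the longer calendar raises power with 4,000 subjects to about 90%.

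**What to change.** In protocol section 11.4.1, replace the 2.5-year derivation with the v1.3 calendar (3.5 years of enrolment plus 1 year). State one trigger at half of the information expected at the planned end of study:

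- preferably about 164 adjudicated primary events, half of the about 328 expected under the design rates with 5% dropout per year; or
- about 4,890 person-years, half of the 9,778 obtained with the 8/9 factor.

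Delete the gloss that ties the look to the end of a 2.5-year enrolment. State that the figure assumes 4,000 subjects, so that it is re-derived if the target or dates change again. Check that the IDMC manual and the interim analysis protocol carry the same trigger.

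Do not use 124 events. That is half of the 247 needed for 80% power (4 × (1.96 + 0.84)²/(ln 0.70)² = 247), but the trial ends by calendar and not at 247 events. Since 124/328 = 38%, it would repeat the fault, with a look at about 2.62 years.

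Section 11.1 and SAP section 4 can stay as the record of the sample-size calculation, with a note that the longer calendar gives about 90% power. No change to the final significance level is needed for this point.

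The cost is wording only, and a look some 3 to 5 months later than under the 4,000 person-year rule.
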